## Abstract

**Background:**

More than 3.1 million men in the United States are prostate cancer survivors. These men may improve their physical function, quality of life, and potentially their prognosis by adopting healthier lifestyle habits. The internet provides a scalable mechanism to deliver advice and support about improving physical activity and dietary habits, but the feasibility and acceptability of a Web-based lifestyle intervention and the dose of support necessary to improve health behaviors are not yet known.

**Objectives:**

The Community of Wellness is a Web-based intervention focused on supporting exercise and healthy dietary practices for men with prostate cancer. The objectives of this study were to determine the feasibility, acceptability, and preliminary efficacy of the Community of Wellness Web portal among prostate cancer survivors by conducting a randomized controlled trial (RCT) comparing 4 levels of additive Web-based content and interaction with participants: Level 1 (Teaching; Control), Level 2 (Teaching + Tailoring), Level 3 (Teaching + Tailoring + Technology), and Level 4 (Teaching + Tailoring + Technology + Touch).

**Results:**

Enrollment is ongoing, with 124 enrolled. Study completion (6-month follow-up) is expected by July 2019.

**Conclusions:**

The goal of the study is to identify the level of support that is feasible, acceptable, promotes behavior change, and improves health in men with prostate cancer to inform future efforts to scale the program for broader reach.

**Trial Registration:**

ClinicalTrials.gov NCT03406013; https://clinicaltrials.gov/ct2/show/NCT03406013 (Archived by WebCite at http://www.webcitation.org/73YpDIoTX).

**International Registered Report Identifier (IRRID):**

PRR1-10.2196/11257

## Introduction

Nearly 3 million men in the United States are living with prostate cancer [1], and median survival time following diagnosis for these older men is 16 years [1-3]. During this time, men with prostate cancer might experience adverse effects of aging and persistent side effects of cancer treatment that reduce their physical function, quality of life (QoL), and potentially their prognosis [4-8]. A cancer diagnosis is a *teachable moment* when individuals are often motivated to change behavior to reduce risk of adverse health outcomes and optimize QoL [9-16]. However, advice provided is often inconsistent, and the current standard of care does not support resources for lifestyle behavior change for men with prostate cancer in the United States [17].

For men with prostate cancer, regular physical activity is an excellent strategy to offset age- and treatment-related declines in physical functioning, mental health, and QoL [18]. We and others have shown that when prescribed appropriate physical activity in the form of either aerobic and/or resistance exercise training, it might manage acute and chronic treatment-related symptoms and side effects [10,19-22]. Furthermore, recent observational evidence from our team and others suggests that engaging in sufficient amounts of aerobic activities may reduce prostate cancer progression [11] and prostate cancer–specific death [23-27]. Despite the evidence for physical activity benefits in men with prostate cancer, more than 75% of prostate cancer survivors fail to achieve recommended amounts of aerobic exercise and only 4% engage in any resistance exercise [28]. Prostate cancer survivors may fail to meet the physical activity recommendations because they are not receiving information about the effects of specific types of exercise on the health outcomes that are most important for them. A recent study reported that prostate cancer survivors on androgen deprivation therapy regard a physician’s general recommendation to be physically active as important; however, they are frustrated when providers lack specific knowledge about the type of exercise they should do and lack knowledge on how exercise specifically affects their cancer and related health issues [29-33].

In addition, accumulating evidence from our team suggests that several dietary factors may reduce the risk of prostate cancer progression and death, including greater intakes of cruciferous vegetables, vegetable fat, fish, and cooked tomatoes and lower intake of whole milk and poultry with skin [11,34-43]. Many of these dietary factors (eg, cruciferous vegetables, cooked tomatoes, and whole milk) appear to have specific associations with prostate cancer progression and are not included in general nutrition guidelines for cancer survivors [10]. Furthermore, excess supplementation of vitamins or minerals may increase risk of prostate cancer progression, yet cancer survivors, including men with prostate cancer, report high use of dietary supplements [44,45].

Successful interventions that promote healthy lifestyles can be challenging to scale to the broader population and may not readily reach those persons who are most in need [46]. Center-based lifestyle programs specific to cancer survivors are rare and, if available, tend to be offered only in major academic medical centers in urban areas, whereas home-based interventions have been tested in other cancers [47] including prostate cancer [48]. They are rarely comprehensive enough to address both physical activity and dietary change and raise challenges for tailoring programs to individual needs, maintaining safety and efficacy, and sustaining motivation, especially when counseling is an integral part and would be difficult to maintain indefinitely [49,50]. For optimal engagement, there is a need to provide appropriate content, accommodations, and reinforcement in a way that can successfully promote behavior change [51]. The internet provides a potentially scalable and economical way of delivering lifestyle interventions to cancer survivors [52]. There is 1 Web-based trial (Prostate 8) focused on diet, exercise, and not smoking that has been fully enrolled and will be published soon (NCT02470936). No studies published to date are specific to men with prostate cancer and none simultaneously address physical activity and dietary change while elucidating the types and levels of behavioral support that are effective [53]. For example, men with prostate cancer cite lack of specific guidance for exercise and lack of motivation as barriers to physical activity [33]; thus, interventions that attempt to systematically remove these barriers might be particularly effective but have not yet been evaluated. Another important consideration for future implementation and scalability is identifying the level of *intensity* of an intervention that produces a meaningful benefit. In their translational model of survivorship care, for example, Alfano et al call for trials that evaluate whether or not developing and delivering a survivorship care plan alone for survivors is enough to improve their outcomes or if a more interactive process is necessary [54].

On the basis of the evidence indicating that diet and physical activity habits might offer benefits for men living with prostate cancer, we developed a multisite, national, pilot feasibility study to build and test a Web-based interactive lifestyle management program, the “Community of Wellness,” to provide tools and support for men with prostate cancer to optimize their health through physical activity and diet. It is unclear what types and how much support men may need to make meaningful changes using a Web-based tool; therefore, the objective of this project is to identify optimal combinations of different types and levels of support for diet and physical activity behavior change. To address this objective, we will conduct a randomized controlled trial (RCT) to establish the feasibility and acceptability of the Web-based intervention and explore the preliminary efficacy of levels of support to improve diet and physical activity behaviors, motivational behaviors, and symptoms and side effects associated with prostate cancer and its treatment.

## Methods

### Study Design and Setting

The “Community of Wellness” study is supported by the Movember Foundation and is part of their broader initiative—*TrueNTH USA.* The study is a single blinded, parallel 4-arm RCT comparing 3 levels of increasing behavioral support with a usual care group that receives Web-based general educational information only. Although participants will know which study arm they are randomized to, outcomes are based on self-reported surveys completed by men online; thus, analysts can remain blinded to group assignment. We aim to enroll and randomize 200 men with prostate cancer equally to 1 of the 4 study arms for 3 months. Men complete surveys online at baseline, 3 months (postintervention), and 6 months (3 months postintervention). We will also conduct focus groups after the postintervention follow-up assessment in a subsample of enrolled participants to evaluate elements of usability and acceptability that cannot be obtained via standardized surveys.

### Study Population

The study population is men with a history of prostate cancer. Men are eligible to participate if they self-report receiving a prostate cancer diagnosis, are aged 18 years or older, able to read English on a computer screen, and have a personal device that has internet access and text messaging and a personal email address. Men are not eligible to participate if they report any contraindications to exercise based on the American College of Sports Medicine exercise preparticipation screening criteria [47] and do not receive a physician clearance to participate in moderate intensity physical activity. In addition, men who are currently receiving chemotherapy or radiation therapy will be required to receive a physician clearance before enrollment. Eligibility is assessed via phone screening, and eligible men provide consent online.

Consented participants are randomly assigned to 1 of the 4 Levels of intervention (n=50 per group). Recruitment is based out of 4 academic medical centers (Oregon Health & Science University [OHSU, primary study coordinating center], University of California San Francisco [UCSF], University of Colorado Denver [UC Denver], and Emory University). The primary recruitment approach will use patient databases to identify potential participants who will be mailed a letter and study brochure that directs them to contact research staff at the coordinating center to learn more about the study. In addition to this approach, clinics will have study brochures in waiting and exam rooms. Once deemed eligible, men are emailed a link to provide consent and complete surveys online, and once these are completed, they receive a separate link to access the Web portal where they will access their randomized level of the intervention. The study is approved by 3 institutional review boards at OHSU, UCSF, and UC Denver and is under review at Emory University.

### Study Arms

Our overarching goal is to support healthy diet and physical activity among men with prostate cancer; thus, we aim for a program that has strong acceptability and feasibility and which is also effective and can be broadly disseminated. The intervention was informed by the social cognitive theory that focuses on individual behavior change by including intervention components that addressed key constructs of self-control, expectations, and behavioral capability by including information about exercise for cancer survivors and tailored recommendations for diet and exercise, observational learning by including exercise videos and diet recipes, reinforcement by including technological components that provided feedback on goals, and promotion of self-efficacy through the use of health coaches [55]. We also incorporated techniques to promote user engagement with digital interventions by including credible information that was tailored to address the health needs of prostate cancer survivors and their desire to have information about health behaviors that are specific to their disease [33] as well as the use of prompts to facilitate motivation [56]. The intervention is structured around supporting 3 specific physical activity recommendations (aerobic, strength, and flexibility/balance exercise) that align with recommendations from the American College of Sports Medicine and 8 dietary recommendations (intake of cruciferous vegetables, cooked tomatoes, fish, processed meat, poultry with skin, whole milk, vegetable fat, and vitamin supplements) that are consistent with the scientific literature on diet and prostate cancer at the time of the study’s development (approximately 2016).

**Table 1 table1:** Intervention components available from the Community of Wellness Web portal by level.

Level^a^	Type of support	Component^b^
1	Teaching; educational information about exercise and diet, presented in a static website format	Exercise guidelines for prostate cancer survivors^b^; diet guidelines for prostate cancer survivors^b^; exercising safely with various health issues^b^; and resources (exercises and recipes for recommended foods)^b^
2	Tailoring; Level 1 plus personalized exercise and diet advice	Personalized exercise prescription and diet recommendation^b^ and videos of recommended exercises^b^
3	Technology; Levels 1 to 2 plus technology support	Text messaging to support and reinforce diet and physical activity behaviors; Fitbit Alta plus physical activity progress reports based on physical activity tracker data^b^; and self-report log of progress toward diet and exercise goals^b^
4	Touch; Levels 1 to 3 plus *live* personal support from a health coach	Phone consult with diet and exercise coaches (30 min each) and ongoing Web-based (via email) support from diet and exercise coaches

^a^Each progressive level receives the intervention components of the level before it; for example, a participant randomized to Level 3 technology receives all the components of Levels 1 to 3 but not 4.

^b^Items available on the Web portal.

Each study arm provides additive levels of behavioral support accessed via a Web portal that can be viewed on multiple computing devices including a personal computer, tablet, or smartphone. The 4 study arms are as follows: Teaching (Level 1; usual care control), Tailoring (Level 2), Technology (Level 3), and Touch (Level 4). Each level receives the tools and resources of the prior level such that Level 4 participants receive the most intervention components and is the only level to include additional personal contact via phone and email between a participant and a health coach. Table 1 summarizes the intervention components that are accessible to men who are randomized to each of the 4 arms.

The intervention components are described in more detail below.

#### Level 1: Teaching

This level contains Web-based static information about physical activity and diet advice for men with prostate cancer.

#### Level 2: Teaching + Tailoring

This level contains the content in Level 1 plus personalized exercise and diet advice. Men in this group answer a series of questions about their exercise and diet habits and preferences at baseline to generate a personalized exercise and diet program. In addition, men in this group receive access to instructional exercise videos. The exercise programs generated for men are based on the evidence for exercise as a strategy to manage side effects and symptoms for prostate cancer, slow prostate cancer progression, reduce overall mortality risk, and/or improve physical functioning [9,10,19-21,27,57-62]. Tailoring of each program is based on a man’s response to a series of questions that ask about his health status, current and past prostate cancer treatments, health goals for exercise, current participation in aerobic and strengthening types of physical activity based on responses to the Rapid Assessment of Physical Activity questionnaire [63], resources for exercise (ie, access to an exercise facility, home exercise equipment, etc), and time available for exercise. A man’s stated health goals dictate the mode (aerobic and/or resistance training) of exercise training in his prescription; his exercise resources further dictate the type of training selected for his program (ie, machine weights in a gym vs resistance bands at home); his health status, prostate cancer treatments, and current exercise levels dictate the exercise intensity of his prescribed program; and his available time dictates the frequency and length of prescribed training sessions (Figure 1).

Similarly, we assess men’s usual dietary habits using a validated food frequency questionnaire (FFQ) [64], benchmark his usual diet against 8 dietary recommendations we have developed based on the literature, and provide tailored advice on how he can improve his diet. Our recommendations are based on a review of the literature on diet and prostate cancer progression as of August 2016 [16] and also take into consideration recommendations from the American Cancer Society and dietary guidance provided for prevention of major chronic illnesses (eg, American Heart Association and American Diabetes Association recommendations). See Figure 2 for an example of how information would be provided back to participants about whether or not they are meeting dietary recommendations.

After receiving their personalized advice and access to instructional videos, men do not receive any further feedback to support behavior change.

#### Level 3: Teaching + Tailoring + Technology

This level contains the content provided in Levels 1 and 2 plus technology support for changing physical activity and diet habits. Men in this group are asked to log their diet and exercise behavior through the website and can view their progress over time. These men also receive a physical activity tracking device (Fitbit Alta; mailed to the participant) that interfaces with the Web portal and educational and motivational text messages about healthy diet and physical activity habits. Men are encouraged to use the Fitbit as a motivational tool and they can be synched to the portal where men can see displays of their time spent in physical activity, distance covered, and steps. Men do not receive separate physical activity goals related to use of their Fitbit. A total of 90 automated text messages are sent over the entire intervention period, averaging 4 texts per week. About 25% (23/90) of text messages ask the participant to reply to the message to promote an interactive experience.

**Figure 1 figure1:**
[figure not shown]
Algorithm to generate a tailored exercise prescription based on participant input. *Current physical activity determined by answers to the Rapid Assessment of Physical Activity (PA) questionnaire that determines how regularly men participate in moderate or vigorous aerobic exercise and resistance exercise. Men who are meeting current PA guidelines may be prescribed a vigorous intensity program, men who engage in aerobic or resistance exercise, but not enough to meet guidelines may be prescribed a moderate intensity program, while men who are inactive or sedentary will be prescribed a low intensity program.

#### Level 4: Teaching + Tailoring + Technology + Touch

This level contains the content provided in Levels 1 to 3 plus interactive support via phone and online with research staff to support diet and exercise behavior change. Men in this group have the option to receive 2 30-min phone consultations, 1 with an exercise coach (certified athletic trainer) and 1 with a diet coach (registered cancer dietician). Participants also have the ability to receive ongoing advice from coaches via email sent through the Web portal. Men can email either coach as little or as often as they would like for the 12-week intervention period. Figure 3 provides a screenshot of a Level 4 dashboard.

### Randomization Assignment

The randomization scheme was for 4 arms, stratified by site (up to 5 sites were accommodated), with a block size of 4. The randomization sequence generation and randomization assignments were handled by study staff who were blinded to participants’ identifiers or any screening information. The randomization allocation sequence was generated by a staff statistician at the UCSF and shared with coinvestigators and team members at UCSF. Screening and enrollments were handled centrally by study team members at Oregon Health & Sciences University (OHSU). As patients enrolled, OHSU staff would request randomization allocations by site from UCSF staff by email; allocations were obtained by UCSF staff (who were blinded to patient identifying information) from the sequence following a consecutive order and communicated back by email to OHSU, typically within 24 hours. OHSU study staff then provided the appropriate Web intervention to each participant, based on the assignment received from UCSF. The randomization was done using *proc plan* in SAS v9.4.

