## Results

Development of the Community of Wellness website is complete, has been beta-tested, and is currently being evaluated in the RCT. This RCT is open for enrollment (ClinicalTrials.gov NCT03406013) and anticipates completing enrollment by the end of 2018. Recruitment is open at 3 of the 4 academic medical centers (OHSU, UCSF, UC Denver, and Emory University [pending]) with the target population of 50 men enrolled at each site for a total of 200 subjects. OHSU achieved their recruitment goal and enrolled 50 men. UCSF is actively recruiting, with 27 men currently enrolled, and UC Denver is just open. We expect to fully accrue to the trial by January 2019, with final data collection complete by July 2019.

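### With one block size of 4 for 4 arms within site, the central team that enrolls and sees every allocation can foresee the last place in each full block

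*Protocol article*

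**What the plan says.** All references are to the protocol article.

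- **Scheme.** Randomization Assignment: "The randomization scheme was for 4 arms, stratified by site (up to 5 sites were accommodated), with a block size of 4". No second block size and no random variation of block size is described.
- **Who enrolls.** The same section gives screening and enrollment for all sites to a central team at OHSU. That team asks UCSF for an allocation by site. UCSF takes it "from the sequence following a consecutive order and communicated back by email to OHSU, typically within 24 hours".
- **Who delivers.** "OHSU study staff then provided the appropriate Web intervention to each participant, based on the assignment received from UCSF".
- **Who holds the list.** The sequence was "generated by a staff statistician at the UCSF and shared with coinvestigators and team members at UCSF". The stated safeguard is that sequence generation and assignment were "handled by study staff who were blinded to participants’ identifiers or any screening information".
- **Blinding.** Study Design and Setting says that participants know their arm and complete the outcome surveys themselves online; "thus, analysts can remain blinded to group assignment".
- **Pathway.** Study Population describes phone screening for eligibility, online consent, random assignment of consented men, and portal access after the online consent and surveys.
- **Site size and progress.** Results gives a target of 50 men at each of four sites. OHSU is complete, "UCSF is actively recruiting, with 27 men currently enrolled", UC Denver has just opened and Emory is pending.

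**The concern.** When the block size equals the number of arms, each block is one ordering of the four levels. Anyone who sees a site's past allocations can strike off the levels already used in the current block. Here the people who see that history are the people who speak to men at phone screening and manage their entry. The safeguard in the article is placed on the UCSF allocators, who do not enroll. It does nothing about what OHSU staff can predict.

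A screener who expects the next place to be the coach level or the static-website level could, without intending to, adjust encouragement, timing or the pursuit of physician clearance. Motivation is a trait a screener can sense on the phone, and it plausibly drives dropout, log-ins and self-reported behavior change. Participants know their arm and report their own outcomes, so concealment of the next allocation is one of the few protections left for the comparisons between levels.

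**Working it through.** The article gives no figure for predictability, so there is none to reproduce.

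**Inputs.** 4 arms, equal allocation, block size 4 within site (Randomization Assignment); 50 men per site at 4 sites, 200 in total (Results). Assumption: the guesser knows or infers the block size and has that site's past allocations.

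**Within one full block.** With k levels still unused in the block, the best guess is right with probability 1/k:

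- 1st place: 1/4
- 2nd place: 1/3
- 3rd place: 1/2
- 4th place: 1 (certain)

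The mean is (1/4 + 1/3 + 1/2 + 1)/4 = (25/12)/4 = 25/48 = 52.1%. Chance is 1/4 = 25%. The share known with certainty is 1/4 = 25%.

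**Per site of 50.** 50 = 12 × 4 + 2, so there are 12 full blocks and 2 extra places.

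- Certain allocations: 12 per site, 4 × 12 = 48 of 200.
- Expected correct guesses: 12 × 25/12 + 1/4 + 1/3 = 25.58 per site; 4 × 25.58 = 102.3 of 200 (51.2%), against 50 by chance.

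**Larger fixed blocks, size known to the guesser (exact enumeration; the best guess is the arm with most places left).**

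| Block size | Correct guesses | Certain |
|---|---|---|
| 4 | 52.1% | 25.0% |
| 8 | 47.0% | 14.3% |
| 12 | 44.1% | 10.0% |
| 16 | 42.1% | 7.7% |

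**Randomly varying blocks, simple guesser (simulated 50-man sites, 5,000 repetitions).** The guesser names the least-used arm at the site, breaks ties at random and does not use the block size.

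| Blocks | Correct guesses |
|---|---|
| 4 only | 51.1% |
| 4 or 8 | 47.7% |
| 4, 8 or 12 | 45.3% |
| 8 or 12 | 44.2% |

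The 51.1% for blocks of 4 agrees with the exact 51.2% above.

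**Do mixed blocks remove the certain calls?** Not for someone who knows the set of sizes. Take blocks of 4 or 8. If the first block is an 8, the chance that its first four draws are all different is (6/7)(4/6)(2/5) = 0.229. A repeated level therefore appears within four draws with probability 1 − 0.229 = 77%. The repeat reveals the 8 and makes its eighth place certain.

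**Without the history.** An enroller who cannot see past allocations is back to 25%, whatever the block size.

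**The case against.** Several points on the other side stand.

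- **Knowledge of the block size.** The article does not say that OHSU staff were told it. It can be inferred once a few runs of four different levels have gone by at a site, but 52% describes an attentive guesser and is an upper-end figure.
- **Limited control of timing.** Men are randomized after consent and complete the online steps on their own schedule. A phone screener does not fully control who takes which place. This weakens the opportunity to steer but does not remove the foresight.
- **Modest remedy.** Varied blocks help a little and do not abolish certain calls, as the working shows.

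A reader might go further in three ways that the article does not support.

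- **That analyst blinding is broken.** No section says who the analysts are or that they are among the UCSF staff given the sequence. Blocks of 4 do not unblind an analyst who lacks the list.
- **That sharing the list at UCSF is itself a route to selection because UCSF recruits.** The UCSF staff who handle the assignments are described as blinded to identifiers and screening information, and enrollment is done at OHSU. The access is wider than it needs to be, but no UCSF role in screening or enrolling is described.
- **That the primary outcomes are biased.** Statistical Power treats accrual, recruitment and 3-month retention as single overall proportions. Moving men between levels need not change them.

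**Conclusion.** The point holds for predictability. One block size equal to the number of arms, applied within site and combined with an enrolling team that receives the allocation history, lets an attentive enroller foresee 12 of 50 allocations per site with certainty. The same enroller can guess about half of all allocations, twice the chance rate. This assumes that the enroller knows or infers the block size and follows each site separately. The article does not show that anyone did so.

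What is exposed is the set of comparisons between levels: dropout across arms, log-ins by level, and change in behavior score against Level 1. The size of any resulting bias cannot be calculated from the article, because it depends on how far foresight was acted on. The overall accrual and retention estimates are not threatened. Whether analysts are blinded remains unstated rather than contradicted.

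**What to change.** Allocations already used, including all of OHSU's, cannot be changed. For those not yet used (the rest of UCSF, UC Denver and Emory):

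1. Regenerate the list with randomly varying block sizes, for example 4, 8 and 12, and do not disclose the sizes.
2. Restrict the list to the statistician who generates it and the person who releases allocations. Keep it from recruiting and analysis staff.
3. Where feasible, have different OHSU staff screen men from those who receive and deliver the allocation, so that screeners do not see the history.
4. State whether enrollers knew the block size for the allocations already made, and that the analysts did not have the sequence, if that is so.

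Item 1 alone takes a simple guesser from about 51% to 45% and reduces certain calls without eliminating them. Item 3 addresses the source, since a screener without the history is left with 25%.

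The cost is one new list, a restricted file and some reassignment of tasks at OHSU. The statistical price is slightly more imbalance between arms within small sites. If recruitment stops partway through a block, two arms can differ by at most 1 man with blocks of 4, and by at most 3 with a block of 12.
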